## Abstract

**Introduction:**

Cardiac rehabilitation programs face the challenge of suboptimal participation, despite being a level Ia recommendation. Cardiac telerehabilitation, with its potential to engage patients who might otherwise not show interest, necessitates the adaption of existing center-based cardiac rehabilitation programs to facilitate rehabilitation at home. REHAB + is a mobile cardiac telerehabilitation program cocreated with patients and rehabilitation centers, aiming to future-proof cardiac rehabilitation and improve accessibility. The REHAB + application enables users to remotely communicate with their coach, receive on-demand feedback on health goal progression, and reduces the need for frequent in-person meetings at the cardiac rehabilitation center. The REHAB + study seeks to compare patient-related outcomes and characteristics of patients between those offered the option to participate in cardiac telerehabilitation and those attending center-based cardiac rehabilitation over a twelve-month period.

**Methods:**

The REHAB + study is a multicenter, prospective, matched controlled, observational study that includes (N)STEMI patients eligible for cardiac rehabilitation. We aim to enroll 300 participants for cardiac telerehabilitation and 600 for center-based cardiac rehabilitation. Participants opting for cardiac telerehabilitation (REHAB+) will be matched with center-based cardiac rehabilitation participants. Additionally, characteristics of patients unwilling to participate in either center-based rehabilitation or telerehabilitation but are willing to share their demographics will be collected. The primary endpoint is quality of life measured with the SF-36 questionnaire at three and twelve months, with patient-related characteristics driving intervention choice as the most important secondary endpoint. Secondary endpoints include physical activity, modifiable risk factors, and digital health experience. The trial is registered at clinicaltrials.gov with registration number NCT05207072.

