Previous research (7) explored the factors leading to non-participation in a telerehabilitation trial. Results show that factors leading to non-participation in this telerehabilitation trial (7) are associated with a worse cardiovascular risk profile (e.g., high age, a higher prevalence of modifiable risk factors, lower exercise capacity), lower prevalence of high education, lower prevalence of employment, and shorter travelling distance to the nearest hospital. Our hypothesis matches these results i.e., that patients not interested in CTR have a worse cardiovascular risk profile, a lower social economic status, and live closer to the nearest hospital than patients who are interested. The REHAB + study is the first large (>150 patients) multicenter and multinational prospective observational study to evaluate the effect of cardiac telerehabilitation in daily practice. It provides the possibility to gain experience with implementing cardiac telerehabilitation. Our study design differs from previous research by its size, design (observational instead of RCT) and inclusion in different European centers and countries. It provides beneficial information about patient characteristics and results. The aim of the REHAB + trial is to identify which parameters influence the decision to participate in center-based CR, CTR, or decline participation in CR. We will compare quality of life, physical activity, and modifiable risk factors before, during and after program completion. We expect an improvement in quality of life, specifically the physical component, in both center-based CR and CTR.

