#### Questionnaires

2.7.1

Participants evaluate quality of life at baseline, three months and twelve months using the 36-Item Short Form Health Survey (SF-36) version 2.0. Each participating center used a validated version translated to the local language (34, 35). The questionnaire provides a score on eight domains. These translate to a physical component score and a mental component score. Domains mostly related to the physical component score has the most pure interpretation for chronic medical conditions (36).

A coach and cardiologist assess physical fitness at baseline using an exercise test. The participant completes the exercise test by exerting their maximal workload. However, the test stops prematurely if the participant exhibits angina. Physical activity is evaluated for all participants using the International Physical Activity Questionnaire-Short Form (IPAQ-SF) (37, 38). The IPAQ-SF is a 7-item questionnaire, which allows the calculation of metabolic equivalents (METs score) using self-reported physical activity intensity and frequency.

The modifiable risk factors are documented during hospitalization, from which baseline data on the use of tobacco products is extracted. Patients fill out the Fagerström test, testing nicotine dependency at baseline, three months and twelve months. The Fagerström test is a validated (39, 40), 5-item questionnaire with a scoring system that categorizes dependency on nicotine in four categories (barely dependent, to lightly dependent, to moderately dependent, to strongly dependent).

CTR participants receive the e-Health Impact Questionnaire (eHIQ) at baseline, three months and twelve months, evaluating their previous general health experience (11-item questionnaire) and the digital health experience of the REHAB + app (15-item questionnaire). Center-based CR participants only receive the general health experience section. The eHIQ is validated for Dutch participants (41). An official translation agency translated the eHIQ into Spanish for the Spanish centers with permission of the original authors.

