### Sample size calculation

2.8

The sample size calculation is based on an expected increase in quality of life after one year, specifically the physical component score change of the SF-36 questionnaire V2.0. Previous research (42) found baseline quality of life physical component score of 48.4 + - 5.8 at program initiation and 53.3 + - 3.9 after 12 months. We estimated an increased score to 55 + - 7.0 for CTR patients. The sample size calculation, using the Hotelling Lawley Trace test, resulted in a sample size of n = 268 per group (power = 0.8 and alpha = 0.05). Assuming 10% withdrawal or incomplete data, we aim for n = 300 participants per group. We expect a 1:2 ratio of participants choosing CTR vs. center-based CR. We aim to continue inclusion until 300 participants are included in the CTR group, with enough participants to match in center-based CR (600). This will likely result in 300 participants per participating CR center (100 participants choosing CTR and 200 participants choosing center-based CR).

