### Statistical analysis

2.9

Continuous data will be analysed with the independent T-Test (or Mann-Whitney U test for non-normal distribution of data). Categorical data will be analysed using the chi-squared test (two groups) or ANOVA (> two groups). The One-way ANOVA test (or Kruskal Wallis test for non-normal distribution of data) will be used to analyse >two continuous data categories. The impact of multiple variables on allocation is analyzed using the multinomial regression analysis. All statistical tests are considered significant at P < 0.05. Statistical analysis will be performed on the latest version of IBM SPSS Statistics or R.

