### Limitations

3.1

Although the implementation of CTR might be as (cost-) effective as center-based CR, there could be a learning curve at the start of this newly implemented CR program. Center-based CR and CTR could vary in frequency, intensity, duration and initiation of the program. However, this could be a strength when patients are allowed to compare the programs and choose which one fits them best. It could lead to improved participation in CR.

The coaches of the REHAB + application will use the remote communication feature to frame motivational texts or video’s to benefit long-term uptake of the exercise program. The ability to track behavioral health goals in CTR is a feature that lacks in center-based CR. The frequency of in-person exercise training sessions might initially favor center-based CR short-term on quality of life and exercise goals. However, the ability to track health behavioral goals and the ability to use the application for over nine months might favor CTR long-term.

Local differences may occur due to the unique features that each CR center might implement additionally to local or international guidelines. A learning curve for CR centers without experience with CTR is expected to occur. The nature of treatment allocation of REHAB + results in selection bias, which does resemble daily clinical practice. There is also the possibility that the expected ratio of 1:2 center-based CR and CTR will not be met, as participants have the freedom to choose their CR modality.

Due to the nature of the study, in which clinical practice is closely evaluated, the use of a follow-up exercise test to evaluate physical activity after CR was not feasible. Therefore, the choice for a less rigorous method of physical activity evaluation was chosen, namely by questionnaire which could have recall bias. Participants will have a baseline exercise test to evaluate their physical condition.

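### The primary endpoint is SF-36 quality of life at two time points with no score named, while the study is sized only for the physical component score at one year

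*Protocol article*

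**What the plan says.** - **Abstract, Methods.** "The primary endpoint is quality of life measured with the SF-36 questionnaire at three and twelve months". No component score or domain is named, and neither time point is given precedence. What drives the choice of program is ranked there as the leading secondary endpoint.
- **Section 2.7.1, Questionnaires.** On the SF-36: "The questionnaire provides a score on eight domains. These translate to a physical component score and a mental component score".
- **Section 2.8, Sample size calculation.** The calculation rests on the expected gain after one year, "specifically the physical component score change of the SF-36 questionnaire V2.0". It gives reference PCS values at program start (48.4, SD 5.8) and at 12 months (53.3, SD 3.9), and an assumed 55 (SD 7.0) for telerehabilitation. It names the Hotelling-Lawley trace, power 0.8 and alpha 0.05, and arrives at 268 per group, raised to 300 for 10% loss. It gives no three-month value and no mental component value.
- **Section 2.9, Statistical analysis.** Continuous data get a two-sample t-test, or Mann-Whitney where they are not normal. "All statistical tests are considered significant at P < 0.05". The Hotelling-Lawley test does not reappear.
- **Section 3.1, Limitations.** "The frequency of in-person exercise training sessions might initially favor center-based CR short-term on quality of life and exercise goals". The next sentence says that goal tracking and long use of the app might favor telerehabilitation in the long run.
- **Introduction.** "The aim of the REHAB + trial is to identify which parameters influence the decision to participate in center-based CR", telerehabilitation or neither. The comparison of quality of life follows in the next sentence.

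**The concern.** The abstract holds the article's only definition of the primary endpoint, and it does not match what section 2.8 powers. Read with section 2.9, a reader would test SF-36 quality of life at three months and again at twelve, each at 0.05, and treat either as the primary result. Two things are then at stake.

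1. The 5% error rate set in section 2.8 belongs to one comparison, not to the primary endpoint as defined. A primary claim could rest on a time point, or on a score, that was never sized.
2. The pattern that section 3.1 raises would give one primary result for center-based rehabilitation and another for telerehabilitation. Both could be significant, with nothing in the article to say which one answers the question.

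**Working it through.** **Step 1: what the stated sample size covers.** Inputs from section 2.8: difference 55 − 53.3 = 1.7; SD 7.0; alpha 0.05; power 0.80. Sidedness is not stated, so two-sided is assumed.

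n per group = 2 × (1.960 + 0.842)² × SD² / difference² = 2 × 7.85 × 49 / 2.89 ≈ 266.2, so 267.

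The exact noncentral-t version gives 268, with power 0.801. With two groups and one between-group contrast, the Hotelling-Lawley trace reduces to this test. Allowing for loss: 268 / 0.90 = 297.8, so 298, which the article rounds to 300.

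Alternatives that do not give 268 (normal approximation):

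| Variant | n per group |
|---|---|
| SD 5.8 | 183 |
| SD 3.9 | 83 |
| SD pooled from 3.9 and 7.0 | 175 |
| SD 7.0, one-sided | 210 |

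A change-from-baseline comparison with SD 7.0 at both times and correlation 0.5 also gives 268, because the SD of change is then √(49 + 49 − 2 × 0.5 × 49) = 7.0. Both routes are a single PCS contrast at 12 months. The figure of 268 is not in error.

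**Step 2: error rate with two primary time points, PCS only.** If the tests were independent, the chance of at least one false positive would be 1 − 0.95² = 9.75%. The same participants are measured twice, so the two test statistics are correlated. The article gives no correlation, so a range is assumed. The chance that |Z| exceeds 1.96 at either time, from a million simulated pairs:

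| Assumed correlation between times | Chance of at least one false positive |
|---|---|
| 0.3 | 9.5% |
| 0.5 | 9.0% |
| 0.6 | 8.8% |
| 0.7 | 8.3% |
| 0.8 | 7.8% |

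**Step 3: what keeping both time points primary would cost.** With a Bonferroni split (alpha 0.025 each) and the same 1.7 and SD 7.0, power at 268 per group falls to about 72%. Restoring 80% needs 324 per group, or 324 / 0.90 = 360 with loss. Section 2.8 makes no such provision.

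**Step 4: direction.** This part needs no correlation. The abstract makes both time points primary. Section 3.1 allows a short-term advantage for center-based rehabilitation and a long-term advantage for telerehabilitation. If both occur, the primary endpoint returns two opposite answers.

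**The case against.** **PCS was plainly intended.** Section 2.8 sizes on it, the Introduction singles out the physical component when stating what improvement is expected, and section 2.7.1 says the physical domains are the most interpretable in chronic disease. This stands as far as the choice of score goes. A reader might infer from the unnamed score that the mental component and all eight domains are primary too. With assumed correlations, that would put the error at about 15 to 18% for two component scores at two times, and about 31 to 47% for eight domains at two times. The documents do not support that reading: section 2.7.1 only describes how the instrument is scored, and nowhere are these scores made separate primary tests. Intending PCS does not, however, remove the second time point.

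**The Hotelling-Lawley trace could be one global test at 5%.** It could, but section 2.9 does not carry it into the analysis and lists separate two-group tests instead. A global rejection would also not say which time point, or which direction, is the primary result.

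**A hierarchy may sit in an analysis plan that is not shown.** That is possible, and its absence from an article is not itself a fault. The point rests on what the article does state: two primary time points, one sized outcome, and 0.05 throughout.

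**Opposite directions are not predicted.** Correct. A reader might take section 3.1 as a forecast, but it says only that each program might be favored and does not name three months. The Introduction expects improvement in both groups. A differing time course would also be informative in itself. The possibility is enough to show that a lead time point is needed.

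**The study is observational and declares selection bias.** True, but it sets an alpha, a power and a primary endpoint, and concludes that it will compare effectiveness, so the endpoint still has to be unambiguous.

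**Conclusion.** The concern holds in a limited form. The primary endpoint as defined (SF-36 at three and twelve months, score unnamed) differs from the one that is sized (PCS at one year), and every test runs at 0.05. On the reading closest to the text, PCS at two times, the chance of a false-positive primary result is about 8 to 9% instead of 5%. This assumes normal test statistics and a correlation between times of 0.5 to 0.7; across 0.8 to 0.3 it is 7.8 to 9.5%. It would be higher if the mental component score were also counted as primary, which the article does not say. The lack of a lead time point matters at least as much, because the two results could disagree in direction. The sample size is sound for the single 12-month comparison. The differing statements of the main aim in the Introduction and the abstract are a minor inconsistency of wording.

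**What to change.** Before any outcome analysis, and with the date recorded, name one primary endpoint: the difference between telerehabilitation and center-based rehabilitation in SF-36 PCS at 12 months, tested two-sided at 0.05. This is the outcome section 2.8 sizes, and 268 per group (300 with loss) reproduces as an unadjusted two-sided comparison. Make three-month PCS, the mental component score and the domain scores secondary. Adjusting for baseline PCS, which is already collected, is an optional gain and is not part of the stated sizing. Reword the aim in the Introduction so that it agrees with the ranking in the abstract.

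The cost is wording in the protocol, the analysis plan and the registry entry, with no change to enrolment or data collection. The downside is that a three-month or mental component result can no longer be claimed as primary. If the sponsor prefers to keep both time points primary, an adjusted or ordered testing rule is needed; with a Bonferroni split, the sizing would be 324 per group before loss.

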**Discussion:**

The REHAB + trial is unique by offering patients freedom to choose between cardiac telerehabilitation and center-based rehabilitation. The integration of digital components into cardiac rehabilitation has the potential to complement behavioral change strategies for specific patient groups. Offering patients the option of cardiac telerehabilitation next to center-based rehabilitation could enhance overall cardiac rehabilitation participation rates.

## Introduction

1

Cardiac rehabilitation (CR) programs reduce the risk of cardiovascular hospitalization, future myocardial infarction, and cardiovascular mortality, while also improving quality of life (1–3). However, participation in CR programs remains low, despite strong evidence that outline their benefit (3–7).

Previous research (8–11) outlined various categories that might discourage patients from participation, which include practical, systemic, personal and COVID-19 related barriers. Practically, patients might lack the means to commute to the CR center, lack the time to attend CR due to work or personal scheduling issues, or lack the financial means for regular transportation. Personally, patients could misconceive the severity of coronary heart disease and underestimate the effectiveness of CR as a therapy for cardiovascular risk reduction. Some patients try a personal approach to tackle risk factors, but these often lack the multidisciplinary strategies that CR programs utilize. However, CR programs should implement a personalized approach that could motivate patients into committing to long-term behavioral change. On system-level, the lack of referrals, financial issues, and a one-size fits all approach adversely impact CR program uptake. More recently, the COVID-19 pandemic caused major healthcare changes, which affected clinical and post-clinical care. CR centers closed temporarily during peak infection periods and only partially reopened after policy changes. Nevertheless, some patients remained anxious to commute after reopening, causing delays in CR programs. These delays result in poorer uptake, attendance and completion mitigating benefits (12, 13).

A recent systematic review (14) found no differences in cost-effectiveness for the implementation of home-based CR programs. Dalal et al. (15) offered patients free choice or randomization between home-based CR and center-based CR, and found no differences in anxiety and depression, quality of life, or modifiable risk factors. Two systematic reviews suggest that home-based CR was safe, as no important differences in mortality, cardiac events, exercise capacity, modifiable risk factors and quality of life were found (16, 17) when using the ‘Heart Manual’. In a more recent update of the systematic review on home based interventions, these conclusions remain the same (18). Completely or partially delivering component CR programs might tackle some barriers of participation. Some methods of home-based CR delivery commonly start with attending a few exercise sessions on site (19, 20), after which participants are guided through telephone calling (15, 20, 21), are given educational material (22, 23), or are asked to keep logs on their exercise progression (21).

Telehealth, mHealth interventions and home-based CR are class IIb recommendation (24) in the European Society of Cardiology guidelines. Tele monitoring allows for a change in frequency of face-to-face contact, which in turn could replace home visiting. This might benefit the costs of home-based CR by reducing the number of home visits by nurses (22). Moreover, providing remote feedback on goal progression and providing long-term support might be more feasible in cardiac telerehabilitation (CTR), which are essential components of behavioral change interventions and a class I recommendation (25).

Duration of traditional center-based CR programs usually last for a few weeks to a few months. However, adherence to new behavioral change typically starts after four to six months (25), which is a longer period of time than the duration of most center-based CR programs, but well within the timeframe of CTR. CTR could expand on CR core components by integrating tele coaching, social interaction, tele monitoring and e-learnings (3). Previous CTR research mainly focused on improving exercise capacity (26–28). However, focusing on only one of the core components of CR limits the multidisciplinary approach of CR programs, which means a lot of CTR programs exist as an extension of the exercise program of existing center-based CR rather than a complete CR program.

Remote monitoring offers patients regular reminders to engage in exercise or pursue their health goals more consistently. Long-term tele monitoring might sustain behavioral change (29), such as daily physical activity or non-exercise related core components (e.g., nutritional counseling, psychosocial management or tobacco cessation). Moreover, tele monitoring could support behavioral change strategies (e.g., goal setting, self-monitoring, frequent and prolonged contact), which are essential components for any dietary of physical activity behavioral change (25). Consequently, center-based CR often lack some behavioral change strategies that require long-term follow-up or regular positive reinforcement. Currently, it remains unclear who benefits most from CTR programs (29). Whether home-based CR, let alone CTR might benefit uptake of CR among elderly patients was unproven (30). Recent research (31) seems to suggest that mobile guided CR benefits physical activity in the elderly compared to non-participation, which would underline the importance of whether uptake improves in elderly after CTR implementation. Although older adults are less likely to use mobile technology (32), this is a large proportion of the patients in need of CR. The perception of limited digital skills is a challenge for this population (33). In order to implement mobile technology for older adults, new mobile technology could benefit from a comprehensible digital platform that offers the multidisciplinary approach that center-based CR offers. A simple digital platform might positively reinforce patients using visual cues. Fully remote CR programs lack the social components of center-based CR. If this is perceived as such, remote CR might not be appealing for specific subgroups of patients like women (9).

Previous research (7) explored the factors leading to non-participation in a telerehabilitation trial. Results show that factors leading to non-participation in this telerehabilitation trial (7) are associated with a worse cardiovascular risk profile (e.g., high age, a higher prevalence of modifiable risk factors, lower exercise capacity), lower prevalence of high education, lower prevalence of employment, and shorter travelling distance to the nearest hospital. Our hypothesis matches these results i.e., that patients not interested in CTR have a worse cardiovascular risk profile, a lower social economic status, and live closer to the nearest hospital than patients who are interested. The REHAB + study is the first large (>150 patients) multicenter and multinational prospective observational study to evaluate the effect of cardiac telerehabilitation in daily practice. It provides the possibility to gain experience with implementing cardiac telerehabilitation. Our study design differs from previous research by its size, design (observational instead of RCT) and inclusion in different European centers and countries. It provides beneficial information about patient characteristics and results. The aim of the REHAB + trial is to identify which parameters influence the decision to participate in center-based CR, CTR, or decline participation in CR. We will compare quality of life, physical activity, and modifiable risk factors before, during and after program completion. We expect an improvement in quality of life, specifically the physical component, in both center-based CR and CTR.

